**Objective:**

This study aims to conduct a noninferiority randomized controlled trial comparing OTC HAs with traditional HAs to assess the clinical effectiveness of OTC HAs.

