To address this, we aim to conduct a noninferiority randomized controlled trial (RCT) comparing OTC HAs with traditional HAs. We hypothesize that OTC HAs will demonstrate noninferiority when compared with traditional HAs.

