### Objectives

The primary objective of this study is to compare the effects of OTC HAs and traditional HAs on patients with HL. The primary outcome of interest is functional gain at the conclusion of a 1-year intervention period. Secondary objectives include assessing the impact of OTC HAs and traditional HAs on speech audiometry in both quiet and noisy environments, conducting real-ear measurement (REM), and administering questionnaires to gather additional information.

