## Methods

### Study Design and Setting

In this noninferiority RCT, patients will be randomly assigned to 2 groups. The study will take place at a tertiary hospital in South Korea, serving as a single center for the research. The protocol for this study follows the guidelines outlined in the Standard Protocol Items Recommendations for Interventional Trials statement [10] (Figure 1).

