### Sample Size

The number of participants for this study was determined using G*Power (version 3.1.9.4) software (Institute for Experimental Psychology). The estimated sample size was based on the findings of a previous study [11]. The calculated total sample size was 56 participants, considering an effect size (Cohen *d*) of 0.9, an error probability of .05, and a power (1– error probability) of .95. Therefore, considering an attrition rate of 15%, a total of 64 participants will be recruited, with 32 participants allocated to each group.

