### Statistical Analysis

In the descriptive analysis, continuous data will be presented using means or medians, depending on their normality. Categorical data will be quantitatively presented, including the number and percentage for each variable. For primary and secondary outcome variables, if the normality assumption is met, repeated measurements of analysis of variance will be conducted. If the normality assumption is not met, the Friedman test will be used. Independent variables will be types of HAs and time, while the dependent variables will be outcome variables. Post hoc analysis using Bonferroni correction will be conducted for significant variables. If there is no significant difference in the primary outcome of functional gain between the 2 HAs, it will be considered noninferior.

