## Discussion

### Expected Findings

The purpose of this study is to conduct a noninferiority RCT comparing OTC HAs with traditional HAs to assess the clinical effectiveness of OTC HAs. The expected findings of the study are that OTC HAs will demonstrate noninferiority to traditional HAs in terms of functional gain. This means that OTC HAs will provide similar performance to traditional HAs. Recent research has focused on the clinical effectiveness of personal sound amplification products; however, there is still a lack of studies on the clinical effectiveness of OTC HAs, as they have only recently been introduced. To the best of our knowledge, this study is the first to investigate and potentially confirm the noninferiority of OTC HAs compared with traditional HAs. These findings could have significant implications for the accessibility and affordability of HAs, providing more options for individuals with HL.

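### Noninferiority is to be concluded from a non-significant difference test with no stated margin, so moderate deficits of the OTC device would often pass

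*Protocol article*

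**What the plan says.** The article presents the trial as a noninferiority trial throughout. The abstract's Objective says "This study aims to conduct a noninferiority randomized controlled trial comparing OTC HAs with traditional HAs", Study Design and Setting says "In this noninferiority RCT, patients will be randomly assigned to 2 groups", and the Background ends with "We hypothesize that OTC HAs will demonstrate noninferiority when compared with traditional HAs". The Objectives section fixes the endpoint: "The primary outcome of interest is functional gain at the conclusion of a 1-year intervention period".

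The Statistical Analysis section plans tests of no difference. For primary and secondary outcomes, "if the normality assumption is met, repeated measurements of analysis of variance will be conducted", with the Friedman test as the alternative, and device type and time as factors. The section closes with the only criterion for the main conclusion: "If there is no significant difference in the primary outcome of functional gain between the 2 HAs, it will be considered noninferior".

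The Sample Size section plans 56 participants, raised to 64 (32 per arm) for 15% attrition, "considering an effect size (Cohen *d*) of 0.9", an error probability of .05 and power of .95. It does not call 0.9 a margin, does not say whether the test is one- or two-sided, and gives no SD in dB.

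**The concern.** A noninferiority claim says that any deficit of the new device is smaller than a stated amount. A non-significant test of equality does not show this, because it can also arise when the data are too few or too variable to detect a deficit that matters. With no margin there is no noninferiority hypothesis to test.

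Two further weaknesses follow from the sentence. It takes no account of direction. It also rewards imprecision: the smaller or noisier the trial, the more often the condition is met when the OTC device is truly worse.

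The trial's main conclusion is at stake. Expected Findings anticipates that "OTC HAs will demonstrate noninferiority to traditional HAs in terms of functional gain", and the strengths paragraph says the results could inform clinical practice and policy.

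**Working it through.** **Inputs.** From Sample Size: d = 0.9, error probability .05, power .95, 56 evaluable, 15% attrition, 64 recruited. From Assignment to Intervention Groups: 1:1 allocation. Assumptions: a two-sample t-test at a single time point, with results in SD units because no SD in dB is given. Sidedness is unstated, so both versions are shown.

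**1. The plan's own figure.** With n per arm, the test has 2n − 2 degrees of freedom and noncentrality d·√(n/2). For d = 0.9 and n = 28 the noncentrality is 0.9 × √14 = 3.37.
- One-sided .05: power 0.954, and 28 per arm is the smallest n reaching .95. This reproduces the stated 56.
- Two-sided .05: power 0.911 at 28 per arm; reaching .95 needs 34 per arm (68 in total).

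The stated 56 therefore matches a one-sided 5% t-test. For attrition, 56 × 1.15 = 64.4, which gives the stated 64. Applying 15% loss to 64 leaves 64 × 0.85 = 54.4, about 27 per arm, so 27 to 32 per arm is used below.

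**2. Chance that a truly worse device is called noninferior.** This is P(non-significant) = 1 − power at a true deficit d.

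| True deficit | Two-sided 5%: n = 27 / 28 / 32 per arm | One-sided 5%: n = 27 / 28 / 32 per arm |
|---|---|---|
| 0.3 SD | 81% / 80% / 78% | 71% / 70% / 68% |
| 0.5 SD | 56% / 55% / 50% | 43% / 42% / 37% |
| 0.7 SD | 29% / 27% / 21% | 19% / 17% / 13% |
| 0.9 SD | 10% / 9% / 6% | 5% / 5% / 3% |

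**3. Sensitivity to the repeated-measures analysis.** If the device effect is averaged over three visits with within-person correlation ρ, the effective deficit is d / √((1 + 2ρ)/3). For assumed ρ from 0.5 to 0.9 (28 per arm, two-sided), the false-pass rate is 73-79% at 0.3 SD, 39-52% at 0.5 SD, 12-24% at 0.7 SD and 2-7% at 0.9 SD. The pattern is unchanged.

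**4. Fewer data help the claim.** At a 0.5 SD deficit (two-sided), the pass rate rises from 55% with 28 per arm to 66% with 20 and about 82% with 10. At 0.9 SD it rises from 9% to 21% to 52%.

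**5. What a non-significant result leaves open.** At 28 per arm the 95% confidence interval has half-width t(0.975; 54) × √(2/28) = 0.54 SD. An observed deficit just short of significance is therefore compatible with a true deficit of about 2 × 0.536 = 1.07 SD.

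**6. Power of a proper test at the planned size.** With 28 per arm, true difference 0 and a two-sided 95% interval compared with a margin:

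| Margin | Power |
|---|---|
| 0.9 SD | 91% |
| 0.7 SD | 73% |
| 0.5 SD | 45% |
| 0.3 SD | 20% |

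By the normal approximation n per arm = 2(z₀.₉₇₅ + z_power)² / margin², a 0.5 SD margin needs 126, 170 or 208 evaluable participants in total for 80%, 90% or 95% power.

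**The case against.** The strongest defence is that the sample size already contains a margin. The 56 reproduces as a one-sided 5% t-test at d = 0.9, which is arithmetically the same as a noninferiority test with a 0.9 SD margin. That is correct as arithmetic, but it does not rescue the rule. The article presents 0.9 as an effect size based on a previous study, and the Statistical Analysis section compares no confidence limit with 0.9 or any other value. Nor can the gap be left to an unseen analysis plan: the article states a criterion, and a plan that used a margin would contradict it.

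Some stronger readings are tempting but not supported:

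- A reader might infer that the planned size gives no protection at all, since equal devices pass 95% of the time at any n under a two-sided 5% test. Passing equal devices is the correct outcome, however, and size does matter for large deficits: at 0.9 SD the pass rate is about 10% with 27 per arm against 52% with 10.
- A reader might infer that any clearly worse device would often pass. That holds up to about 0.5 SD, not at 0.7 or 0.9 SD. Without an SD in dB, the document does not allow a judgement on whether 0.3 to 0.5 SD is clinically important.
- A reader might infer that a significant result favouring the OTC device would fail. The sentence says only what follows from non-significance and is silent on the other case.

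It is also fair to object that the rates depend on an assumed test, which is why they are given as ranges.

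**Conclusion.** The point stands and should be corrected before the trial relies on it. The stated rule cannot support a noninferiority conclusion, because it takes non-significance as proof and refers to no margin. Assuming a single-time-point two-sample t-test with 27 to 32 per arm, false noninferiority calls occur about 78-81% of the time at a true deficit of 0.3 SD, 50-56% at 0.5 SD, 21-29% at 0.7 SD and 6-10% at 0.9 SD (two-sided 5%). The one-sided figures are 68-71%, 37-43%, 13-19% and 3-5%. The planned number guards against deficits near 0.9 SD and does so poorly for smaller ones. The sample size arithmetic is not itself in error. That the rule is invalid does not depend on these assumptions; only the size of the problem does.

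**What to change.** Replace the closing sentence of the Statistical Analysis section before enrolment; the article reports that no participants have been enrolled.

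1. State and justify a margin in dB for the difference (OTC minus traditional) in functional gain at 1 year.
2. Declare noninferiority only if the lower limit of the two-sided 95% confidence interval for that difference lies above minus the margin.
3. In the Sample Size section, restate the power that the planned 64 participants give for that margin, with the SD in dB that converts it to SD units.
4. If no justifiable margin is attainable at this size, drop the noninferiority claim and report the difference with its confidence interval.

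Showing the result in both the as-randomised and per-protocol sets would be useful but is optional.

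The rewording needs no new procedures. The cost is that the claim becomes harder to make and the stated power may be less favourable. It would be wrong to assume that no extra participants could be needed: power of about 90% at 28 per arm holds only for a margin near 0.9 SD, and a smaller margin means either a larger trial or a more modest claim.

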### Interventions

The study involves 2 types of HAs: (1) an OTC HA (Jabra Enhance Pro; GN ReSound A/S) and (2) a traditional HA (LiNX Quattro LE561-DRW; GN ReSound A/S). Both HAs used in the study are receiver-in-canal type devices and are manufactured by the same company. The OTC HAs will be fitted by the patients themselves following the manufacturer’s guidelines through a dedicated smartphone app. On the other hand, the traditional HAs will be fitted by a licensed audiologist using the National Acoustics Laboratories–Non-Linear prescription, second generation (NAL-NL2). All HA settings, such as noise reduction, directionality, and feedback cancellation, will be set to their default values.

### Outcome Measurements

The participants will be screened using otoscopy, tympanometry, PTA, and WRS at the first visit (baseline). The participants who pass the screening tests will undergo main tests, including functional gain, REM, speech audiometry, and questionnaires at every visit.

#### Screening Tests

##### PTA Assessment

PTA will be conducted to determine participants’ hearing sensitivity. PTA will be conducted using an audiometer (GSI Audio Star audiometer; Grason-Stadler Inc) with TDH-39 headphones in a double-walled soundproof booth. PTA measurements will be performed in each ear at 0.25 kHz and 8 kHz frequencies following standard procedures [12]. The participants will respond by pressing a button each time they hear the tone. A total of 4 frequency averages (0.5, 1, 2, and 4 kHz) will be calculated.

##### WRS Assessment

WRS provides insight into the participants’ ability to discriminate speech sounds. In this study, WRS will be measured using the same audiometer used for PTA with the TDH-39 headphone in a double-walled soundproof booth. A compact disc player (Yamaha TSX-B232; Yamaha Corporation) will be connected to the audiometer. A total of 25 monosyllabic words [13] at the most comfortable level will be presented. The participants will be asked to repeat the word back to the tester. Percentage-correct scores will be calculated for scoring.

##### Otoscopy

Otoscopy (mini 3000 F.O.; HEINE Optotechnik GMbH and Co) will be used to visually examine structures of the external ear canal, tympanic membrane, and middle ear. The audiologists will insert the cone of the otoscope into the participants’ ear canal.

##### Tympanometry

Tympanometry is an objective, physiological measurement of acoustic admittance of the middle ear as a function of air pressure in a sealed ear canal. A tympanometry will be conducted with a tympanometer (Titan; Interacoustics A/S). The audiologist will insert the probe tip into the participants’ ear canal to measure the air pressure produced by the tympanometer. The tympanogram will illustrate positive and negative variations in air pressure.

#### Main Tests

##### Functional gain

Functional gain will be measured by comparing the hearing thresholds at predetermined frequencies before and after wearing the HAs in a double-walled soundproof booth. The functional gain is theoretically equivalent to the real-ear insertion gain measured through REM. By comparing the functional gain at each frequency with the fitting formula for HA, we can determine the appropriateness of the HA fitting.

##### Speech Audiometry

In quiet conditions, a different list from the Korean standard monosyllabic word lists for adults [13] used in WRS will be used. The testing will be conducted in a free field sound, where 25 target monosyllabic words will be presented at a level of 50 dB HL. The participants will be instructed to repeat the words. The presentation of the target sounds will be positioned 1 meter away from the participant, facing them directly (0°). The percentage of correct responses will be compared before and after wearing HAs. In noisy conditions, the Korean version of the Hearing In Noise Test (K-HINT) will be used [14]. The K-HINT presents speech spectrum noise from front and lateral speakers. For each condition, the noise level is set to 65 dBA, while the speech level is adjusted to measure the reception threshold for speech (RTS). The RTS is determined by measuring the signal-to-noise ratio at which target sentences are perceived correctly 50% of the time. RTS will be compared before and after wearing HAs.

##### REM Assessment

We will use the Aurical Free Fit device (Natus) for REM. After fitting the HAs on the patient, a probe tube will be inserted near the tympanic membrane within a proximity of 6 mm. The REM process involves entering the PTA results into the REM software, selecting the fitting formula (NAL-NL2), and comparing the target gain derived from the fitting formula with the real-ear insertion gain obtained from the REM. During the measurements, participants will hear the stimulus sound from a speaker placed 1 meter away at 0° azimuth. The stimulus sound used will be an Inter Speech Test Signal presented at an intensity of 65 dB SPL, which is comparable with the average level of conversational speech.

##### Questionnaires

The Korean version of the Abbreviated Profile of Hearing Aid Benefit (K-APHAB) consists of a total of 24 items divided into 4 subscales of ease of communication, reverberation, background noise, and aversiveness to measure HL in everyday situations. For each item, a 7-point Likert scale is used (always=1 [99%]; never=7 [1%]). The benefit of the HA will be calculated as unaided scores minus aided scores [15]. The Korean version of the international outcome inventory for hearing aids (K-IOI-HA) is composed of 7 questions designed to subjectively evaluate the performance of HAs solely based on daily use, benefit, residual activity, satisfaction, residual participation restrictions, impact on others, and quality of life. Each item is rated on a 5-point scale, with higher scores indicating greater benefit. The total score ranges from 0 to 35 points [16].

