### Participant Timeline

All participants will undergo in-person assessments over the course of 3 visits conducted at 6-month intervals. During the first visit, the participants will be screened and randomly assigned to 1 of 2 groups: OTC HAs and traditional HAs. Each HA will be fitted according to the guidelines described in the “Interventions” section before conducting the main tests. Subsequently, the participants will undergo main tests and be instructed to use the HA for at least 6 hours daily throughout the intervention period. After 6 months, the participants will return to the clinic for assessments using the same tests from the first visit as an intermediate evaluation. During the final visit (after 6 months), the participants will undergo the same evaluations as during the second visit and return the HAs. If participants experience any discomfort or issues with HA usage during the study period, they will be encouraged to visit the clinic at any time for adjustments (Table 1).

**Table 1 table1:** Timeline for this study.

Outcomes					Screening and baseline			After 6 months			After 1 year			
**Study consent**					✓			—^a^			—			

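### K-IOI-HA is scheduled on fitting day in people who have never worn a hearing aid, and that score enters the device-by-time analysis; separately, its stated range does not fit its items

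*Protocol article*

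**What the plan says.** **The instrument.** Under Questionnaires, the K-IOI-HA "is composed of 7 questions designed to subjectively evaluate the performance of HAs", and the rating is "solely based on daily use, benefit, residual activity, satisfaction, residual participation restrictions, impact on others, and quality of life". On scoring, "Each item is rated on a 5-point scale, with higher scores indicating greater benefit", and then "The total score ranges from 0 to 35 points".

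**When it is given.** Outcome Measurements schedules "main tests, including functional gain, REM, speech audiometry, and questionnaires at every visit". Table 1 agrees: the K-IOI-HA row is ticked at screening and baseline, at 6 months and at 1 year.

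**What happens at the first visit.** Participant Timeline puts screening and randomisation first. Then "Each HA will be fitted according to the guidelines described in the “Interventions” section before conducting the main tests". Then "Subsequently, the participants will undergo main tests and be instructed to use the HA for at least 6 hours daily throughout the intervention period".

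**Who is asked.** Textbox 1 excludes anyone who has used a hearing aid before.

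**How it is analysed.** Objectives lists questionnaires among the secondary objectives. Statistical Analysis assigns primary and secondary outcomes to repeated-measures analysis of variance, or to the Friedman test if normality fails, with hearing aid type and time as the independent variables. It makes no exception for any visit of any outcome.

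**The concern.** A questionnaire that asks how much an aid is used each day, how satisfying it is and what it has done for quality of life can be answered only after a period of wear. On fitting day these participants have worn an aid for part of one clinic visit at most. What they record is a guess or an expectation.

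That would matter little if the score were only filed. The analysis section, however, treats baseline as one of the levels of the time factor. Two consequences follow:

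- A time effect on the K-IOI-HA would mix real change with the step from having nothing to rate to having something to rate.
- The device main effect would average in a visit at which the two devices cannot yet have produced different daily experience.

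A second, independent matter is the stated total range, which does not agree with the number of items and response levels given just before it.

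**Working it through.** **1. Order of events at the first visit**

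| Step | Source |
|---|---|
| No previous hearing aid use | Textbox 1, exclusion criteria |
| Screening, randomisation, fitting | Participant Timeline |
| Main tests, including questionnaires, after fitting at the same visit | Participant Timeline; Outcome Measurements |
| Six or more hours of daily use, over the period that follows | Participant Timeline |
| K-IOI-HA ticked at baseline | Table 1 |

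Text and table agree, so the baseline tick is not a typographical slip. The first K-IOI-HA is completed before any daily use.

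**2. Total range of the K-IOI-HA**

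Inputs: 7 items and 5 levels per item (Questionnaires). The numeric codes are not given; equally weighted consecutive integers and complete answers are assumed. Minimum = 7 × lowest code; maximum = 7 × highest code.

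- Coded 1–5: 7 × 1 = 7 to 7 × 5 = 35.
- Coded 0–4: 7 × 0 = 0 to 7 × 4 = 28.
- A total of 0 to 35 needs items running from 0 to 35/7 = 5, which is six levels, not five.

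The stated 0–35 is not reproduced. The minimum is off by 7, or the maximum is. A maximum of 35 implies 5 points for the top answer, hence 1–5 coding and a range of 7–35.

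**3. Illustration of the dilution**

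The documents give no K-IOI-HA variance, correlation or expected difference, so all of the following are assumptions except the arm size. Arm size: 32 recruited less the plan's 15% attrition, 32 × 0.85 = 27.2, taken as 27. Device difference: 0.7 SD at 6 months and at 1 year, and 0 on fitting day. Correlation between the two later visits: 0.6. Correlation of fitting day with each later visit: r = 0, 0.2 or 0.4. Test: two-sided t-test at 5%.

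Mean of the two later visits:
- Variance (in SD² units) = (1 + 0.6)/2 = 0.8.
- Standardised effect = 0.7/√0.8 = 0.783; power 0.806.

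Mean of all three visits:
- Difference = (0 + 0.7 + 0.7)/3 = 0.467.
- Variance = [3 + 2(0.6 + 2r)]/9.

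Mean of the later visits minus fitting day, which is a form of the time-by-device contrast:
- Difference = 0.7.
- Variance = 0.8 + 1 − 2r = 1.8 − 2r.

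| r | Three-visit variance | Effect | Power | Later-minus-baseline effect | Power |
|---|---|---|---|---|---|
| 0 | 0.467 | 0.683 | 0.693 | 0.522 | 0.47 |
| 0.2 | 0.556 | 0.626 | 0.617 | 0.592 | 0.57 |
| 0.4 | 0.644 | 0.581 | 0.554 | 0.700 | 0.71 |

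Under these inputs, both contrasts that use the fitting-day score have less power than the comparison without it. The size of the loss depends on r and on which contrast is read.

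**The case against.** **Importance.** Questionnaires are secondary. The noninferiority decision rests on functional gain, and no sample size or claim is tied to K-IOI-HA power. This stands in full.

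**The power figures.** The 0.7 SD difference, the correlations and the exact zero on fitting day have no source in the documents. The article does not say that inference rests on a three-visit average: the model has a time factor and Bonferroni post hoc tests, and keeping a baseline score does not prevent a comparison at 6 months or 1 year. At r = 0.4, where the three-visit mean gives 55%, the later-minus-baseline contrast gives 71%. So 55% is the low end for one test, not for the whole plan. This stands, and the figures are illustrative only. It does not give the fitting-day score a meaning.

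**K-APHAB.** A reader might infer that the aided K-APHAB is also completed on fitting day. The documents do not establish that. Benefit is defined as unaided minus aided, so an unaided score is needed at some visit and baseline is the natural one. Table 1 gives a single tick per visit without separating the forms. The placing of main tests after fitting leaves the matter unclear rather than wrong.

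**The range.** A reader might infer that a floor of 0 lets unanswered items entered as 0 pass as valid totals. The article says only that paper records are transferred to Excel. It does not say that blanks become 0 or that the printed range is used as a check, and rules for missing items commonly sit in documents not shown here. Nor does the range error cause the scheduling problem; the two are unrelated. As printed, the range is a descriptive error that changes no participant's score.

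**Conclusion.** The scheduling point holds on the text alone. The K-IOI-HA is given on fitting day to first-time users, and the analysis as written carries that score into the time factor. That the K-IOI-HA is among the outcomes so analysed follows from its place among the secondary objectives and its three ticks in Table 1; the Statistical Analysis section does not name it.

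The direction of the effect is clear: a contaminated time effect, and a diluted device effect if the arms do not differ on fitting day. The illustrated size, 81% against 55–69%, rests on the stated assumptions and applies only to the device main effect.

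The range error also holds, given integer item codes and complete answers, and is minor. Neither point touches the primary outcome. Both should be corrected, but neither puts the trial's main conclusion at risk.

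**What to change.** 1. Remove the K-IOI-HA from the baseline column of Table 1 and from the first-visit main tests. Collect and analyse it at 6 months and 1 year only, and compare the arms at those visits.
2. For the K-APHAB, state which form is used at each visit: the unaided form only at baseline, with benefit at 6 months and 1 year computed against it.
3. State the K-IOI-HA item codes and make the total range agree with them: 7–35 if items are coded 1–5, as the maximum of 35 implies.

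The cost is a few edits to Table 1, Outcome Measurements, Questionnaires and Statistical Analysis, with slightly less burden on participants. What is lost is a fitting-day K-IOI-HA score that has no clear interpretation.
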